#### Process evaluation

A process evaluation with the aid of the RE-AIM framework will be performed to evaluate the diverse intervention components [78]. The RE-AIM model assesses 5 dimensions: reach, efficacy, adoption, implementation, and maintenance. These dimensions interact to determine the impact of the programme. In addition, an adapted version of the framework of Steckler and Linnan will be applied [79]. The following process indicators will be measured in the first follow-up questionnaire (at 6 months after baseline) and continuously during the intervention period: context, recruitment, reach, dose delivered, dose received, satisfaction about the intervention, and fidelity.

#### Economic evaluation

The economic evaluation aims to determine the cost-effectiveness of the intervention compared with usual care from the societal and employer's perspective. Also, the cost-benefit will be determined from the employer's perspective. The time horizon will be one year, similar to the trial. Analyses will be performed according to the intention-to-treat principle. In the main analysis, missing data will be imputed using multiple imputation techniques [80]. Sensitivity analyses will be done to assess the robustness of the results.

First, the total societal and employer's costs will be estimated, and compared between the intervention and control group. The 95% confidence intervals will be estimated using approximate bootstrap confidence (ABC) intervals [81]. Societal costs include all cost measures described in the method section. From the employer's perspective, only costs relevant to the employer are included (i.e. intervention costs, other workplace health promotion costs, and productivity-related costs). For the cost-effectiveness analysis (CEA), incremental cost-effectiveness ratios will be calculated by dividing the difference in costs between both groups by the difference in effects on the primary outcome measures (societal perspective), and outcomes measures relevant to the company (employer's perspective). Bootstrapped cost-effect pairs will be graphically presented on cost-effectiveness planes [82]. Cost acceptability curves will be generated, showing the probability for cost-effectiveness of the intervention at different ceiling ratios. Also, a cost-benefit analysis (CBA) will be performed, in which the incremental intervention and other workplace health promotion costs will be compared to the incremental productivity-related costs.

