### Health problem and target group

The target group for this intervention was specified as all blue collar workers of a construction company. From interviews with the management of the company and from information obtained from Occupational Health Services (OHS) reports it was concluded that the main health concerns for the target population are overweight and MSD. In general, in the construction industry MSD are the primary reason for long-term sickness absence and disability [20,21]. Also the company records show that long-term sickness absence among blue collar workers is mainly caused by MSD.

Especially in professions with heavy physical demands, such as those in the construction industry, muscle fatigue or musculoskeletal discomfort may be perceived during work and may eventually result in musculoskeletal pain [22]. Several work-related physical factors have been identified that can increase the risk of musculoskeletal pain among workers [22-27]. Besides work-related factors, health-related factors, such as obesity may play a role in musculoskeletal pain. Findings of a meta-analysis on the association between obesity and low back pain indicate that overweight and obesity increase the risk of low back pain [5]. In a cohort study of construction workers [28] it was found that MSD represent the most frequent cause of work disability and that obesity increased this risk. Since overweight and MSD are possibly associated, the intervention will aim at addressing these health problems together.

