#### Work-related measures

##### Workplace productivity loss

Sickness absence data (work absenteeism) will be collected from company records. Presenteeism (reduced productivity while at work) will be measured using the WHO Work Performance Questionnaire (WHO-HPQ) [72,73] and the PROductivity and DISease Questionnaire (PRODISQ) [74]. Participants will be asked to complete these questionnaires at 3, 6, 9, and 12 months.

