#### Effect analysis

The effectiveness of the lifestyle intervention will be assessed using a regression analysis with the outcome measures at follow-up (6 months and 12 months) as the dependent variables and adjusting for the baseline levels of the outcome measure. Both crude and adjusted analyses will be performed. Linear and logistic (longitudinal) regression analyses will be performed using SPSS 18.0 (SPSS Inc. Chicago, Illinois, USA). According to the intention-to-treat principle, all available data of the participants will be used for data analysis. For all analyses, a two-tailed significance level of < 0.05 will be considered statistically significant.

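### The cost difference and the cost-benefit result are described as plain between-group differences; adjusting for sickness absence before randomisation, where obtainable, would make them modestly more precise

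*Protocol article*

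**What the plan says.** The Economic evaluation section sets out the estimator in some detail. On costs it says: "First, the total societal and employer's costs will be estimated, and compared between the intervention and control group". The 95% intervals are approximate bootstrap (ABC) intervals. The ratios divide the between-group cost difference by the between-group effect difference. In the cost-benefit analysis, "the incremental intervention and other workplace health promotion costs will be compared to the incremental productivity-related costs". Multiple imputation, cost-effectiveness planes and acceptability curves are also named. No covariate is named for any cost quantity. On robustness there is one general sentence: "Sensitivity analyses will be done to assess the robustness of the results".

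The Effect analysis section treats outcomes differently. It uses regression, "adjusting for the baseline levels of the outcome measure", and adds: "Both crude and adjusted analyses will be performed".

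On the source of absence data, the Workplace productivity loss section says: "Sickness absence data (work absenteeism) will be collected from company records". It gives no look-back period. The Health problem and target group section, reporting the needs assessment, says: "Also the company records show that long-term sickness absence among blue collar workers is mainly caused by MSD".

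**The concern.** Effects are adjusted for their baseline, while costs are described as a simple difference. Productivity-related cost is one of three cost items in the employer's perspective and forms the whole benefit side of the cost-benefit analysis. Absence costs are typically skewed, because a few long absences carry much of the total, and they are likely to persist to some degree within a worker. With about 162 workers per arm, a chance imbalance in workers already prone to absence passes in part into the cost difference.

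Prior absence is the cost component for which a value from before randomisation looks easiest to obtain. Health-care use and sports costs come from three-monthly questionnaires during follow-up, and presenteeism from questionnaires at 3, 6, 9 and 12 months. The sample size rests on body weight alone, so nothing in the design secures precision for costs. Yet the article's Conclusion offers the programme for direct implementation if it proves (cost-)effective.

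**Working it through.** **1. The plan's own figure.** Power calculation section: difference 1.5 kg, SD 4.3 kg, power 80%, alpha 5%; the Effect analysis section makes the test two-tailed. n per group = 2 × [4.3 × (1.960 + 0.842) / 1.5]² = 129.0, rounded up to 130, as stated. Allowing for 20% loss, 260 / 0.80 = 325 against 324 stated, which is rounding. The planned total gives 324 / 2 = 162 per arm. The plan states no figure for costs.

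**2. Assumptions, none from the documents.**
- SD of annual absence: 40 days (range 20 to 60).
- Value of a day: EUR 150 (range 120 to 200).
- Correlation r between prior-year and trial-year absence cost: 0.3 to 0.5.
- n = 162 per arm, because the main economic analysis imputes missing data.

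**3. Precision of the plain difference in mean absence cost.** SE = SD × day value × √(2/n).
- Central: 40 × 150 × √(2/162) = 6,000 × 0.1111 = EUR 667; 95% half-width 1.96 × 667 = EUR 1,307.
- Low: 20 × 120 × 0.1111 = EUR 267. High: 60 × 200 × 0.1111 = EUR 1,333.
- With 130 per arm, the central SE is 6,000 × √(2/130) = EUR 744.

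**4. Effect of adjusting for prior absence.** The SE is multiplied by √(1 − r²). The equivalent gain in sample size is 1/(1 − r²) − 1.

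| r | SE factor | Central half-width (EUR) | Equivalent extra participants |
|---|---|---|---|
| 0 (plain) | 1.000 | 1,307 | – |
| 0.3 | 0.954 | 1,246 | 10% |
| 0.4 | 0.917 | 1,198 | 19% |
| 0.5 | 0.866 | 1,132 | 33% |

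The percentage narrowing depends only on r, not on the SD, the day value or n. At r = 0.1 it is 0.5% and at r = 0.2 it is 2%. These figures concern absence cost. For total cost, the relevant r is the correlation of prior absence with total cost, which other cost items may lower.

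**5. Size of a chance imbalance.** An imbalance of one SE in prior absence shifts the plain difference by r × SE. At the central SE this is 0.3 × 667 = EUR 200 to 0.5 × 667 = EUR 333 per worker. Over the full assumed ranges it is 0.3 × 267 = EUR 80 to 0.5 × 1,333 = EUR 667.

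**6. Cross-check with a different model.** Assume that one long absence lasts 60 to 120 working days at EUR 150 to 250 per day. One extra long-term absentee in one arm of 162 then moves the mean difference by 60 × 150 / 162 = EUR 56 to 120 × 250 / 162 = EUR 185 per worker. This shows how sensitive the difference is to a few workers. It does not show that prior absence would predict who they are.

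**The case against.** - **No bias.** Randomisation is at individual level, so the plain cost difference is unbiased. Chance imbalance is ordinary sampling error, which the bootstrap intervals, planes and acceptability curves are there to show. This stands in full. A reader might infer that the planned cost comparison is invalid; the documents do not support that.
- **Silence in a condensed article.** The article never calls the cost analysis unadjusted. A fuller plan may name covariates, and sensitivity analyses are announced. This stands in part: the section describes the estimator step by step as a between-group difference, and unspecified sensitivity analyses would not change the main estimate.
- **Baseline absence may already be covered.** Sickness absence is listed among the secondary outcomes, so the Effect analysis section would adjust it for baseline when it is analysed as an outcome. That is a fair reading. It does not reach the monetary difference or the cost-benefit result.
- **Availability is inferred.** A reader might infer that the records hold every worker's absence before randomisation. The needs-assessment sentence concerns blue collar workers as a group. No passage describes a look-back period or individual extraction for that time.
- **Adjustment does not remove the noise.** New long absences that the previous year does not predict remain after adjustment. This stands.

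**Conclusion.** The point holds as a matter of precision. The economic section names no baseline term for the cost difference, the ratio numerator or the cost-benefit result, while the outcome analysis adjusts for baseline. With an assumed r of 0.3 to 0.5, adjusting for prior absence would narrow the absence-cost interval by about 5% to 13%, and by less if prior absence predicts poorly. It would also remove the part of a chance imbalance that prior absence explains.

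A reader might go further and conclude that a few chance absentees would swamp the programme's cost. That cannot be shown. The documents give no programme cost, absence SD, day cost or correlation. Coaching time (40 to 120 minutes per worker in Table 6) is only part of the programme's cost, which also includes the toolbox, housing, printed materials, travel and lost work time. The euro figures above illustrate scale under stated assumptions and do not estimate this trial.

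**What to change.** Where obtainable, add to the company-record extract each participant's absence in the 12 months before randomisation, expressed as a rate for those employed for less time. Pre-specify the main cost difference and the cost-benefit difference as a regression of cost on arm plus prior absence, bootstrapped for the interval, and use the same adjusted cost difference in the ratios. Report the plain difference as supporting. Modelling costs jointly with the baseline-adjusted effects inside each resample is an option, not a requirement. Fix the choice before cost data by arm are seen, because choosing whether to adjust skewed costs afterwards invites selection.

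The cost is a slightly longer extract from a source already planned and a sentence or two of analysis text, with no extra visit or questionnaire. The drawbacks are a possibly incomplete look-back for recent hires and little gain if prior absence turns out to be a weak predictor.

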## Discussion

The aim of this design article was to describe the development and plan for the evaluation of a (lifestyle) programme aimed at prevention and reduction of overweight and MSD among construction workers. This study may be of importance at company level to gain more insight in the effects of preventive measures, and to support decision making on which health promoting activities should be applied. Because the intervention is conducted in the occupational setting a large number of people can be reached, which may have an impact on health outcomes, and company as well as health care costs.

### Strengths

The intervention was designed following the IM protocol. This has been done before in health promotion interventions [83-85]. The development has been conducted with key figures in the organisation as well as with the target group aiming at a better compliance of employers and OHS with the VIP in construction protocol and allowing a scientific approach with consideration of daily practice. If the intervention proves to be effective, then the programme can be directly implemented.

Although the components of the intervention will not be evaluated separately, the process evaluation will give qualitative insight into the success factors, applicability and usefulness of the separate intervention components. Furthermore, the process evaluation outcomes can improve the programme before it will be really implemented.

### Limitations

Creating matrices in step 5 of the intervention mapping protocol was not fully applied, as this is a very time-consuming process. However, since the most important stakeholders were involved during the design of the study, it is expected that the adoption and implementation of the programme is ensured.

Health promotion efforts, particularly those directed to somewhat resistant workers who are at high risk, should preferably be integrated with the provision of improved working conditions. A systematic review of the effectiveness of health promotion interventions in the workplace concluded that participation in workplace health promotion may be increased if interventions also take into account health risks arising from work activities [86]. In this study, not all input of the intended target group has been implemented. This resulted from the fact that the programme has been developed in close cooperation with the management of the organisation, their approval was needed to carry out programme components. It is possible that the programme would have involved other components if only the input of the target group had been taken into account. However, this programme was developed with the intention to be implemented. Therefore, we believe that involving all important stakeholders is necessary.

Finally, this programme has been developed within a specific organisation. In this study, only stakeholders from the participating company and its OHSs were involved in the feasibility assessment and the focus group interviews. Also, a specific characteristic of the construction industry is that most employees are not working at a set location. The optimal infrastructure to reach workers is possibly different in other companies/branches. Therefore, it is possible that the IM process would have led to a different protocol in other workplace settings. This should be taken into account when implementing the intervention outside the construction industry. When generalising this programme to another context, the IM procedure can be applied to modify the existing programme.

## Conclusion

In conclusion, the development of the VIP in construction intervention resulted in a health programme tailored to the needs of construction workers. The method of IM provided the tools to do this systematically. If proven (cost-)effective the programme can be directly implemented, and with minor adaptations in other companies involving blue collar workers or companies that are already offering regular health screening. OHSs or human resource managers may incorporate this method in their usual prevention management. The results of the (process) evaluation will help policy makers decide which elements of the intervention can best be used.

The (cost-)effectiveness and the (implementation) process regarding this intervention will be evaluated. The results of this RCT will be available in 2012.

## Abbreviations

BMI: Body Mass Index; CBA: Cost-benefit Analysis; CEA: Cost-effectiveness Analysis; CVD: Cardiovascular Disease risk; HPQ: World Health Organisation -Health and Work Performance Questionnaire; IM: Intervention Mapping; MSD: Musculoskeletal Disorders; OHS: Occupational Health Services; OP: Occupational Physician; PA: Physical Activity; PAPM: Precaution Adoption Process Model; PHC: Personal Health Coach; PHS: Periodic Health Screening; RCT: Randomized Controlled Trial; SCORE: Systematic Coronary Risk Evaluation; SQUASH: Short Questionnaire to Assess Health Enhancing Physical Activity; TPB: Theory of Planned Behaviour; VIP: Vitality in Practice; WC: Waist Circumference.
